## Aims

This randomized controlled two-arm parallel group superiority study with 1:1 allocation ratio will be conducted with young adults who are 18–30 years of age, exhibit an eveningness chronotype, and demonstrate elevated symptoms in one of the five health domains. Participants will be randomized (1:1) to HABITs alone or HABITs plus Text Message Intervention (HABITs + Texts). There are three aims.

Aim 1 is to assess if adding a text message intervention to HABITs improves sleep health behaviors in the short (post-treatment) and longer term (6-month and 12-month follow-up), relative to HABITs alone. Hypothesis 1 is that, relative to HABITs, participants in HABITs + Texts will (a) report utilizing more sleep health behaviors and (b) establish stronger sleep health behavior habits. We hypothesize that these effects (1a and 1b) will be observed from pre-treatment to post-treatment, pre-treatment to 6-month follow-up, and pre-treatment to 12-month follow-up.

Aim 2 is to assess if adding a text message intervention to HABITs improves sleep and circadian functioning in the short (post-treatment) and longer term (6-month and 12-month follow-up), relative to HABITs alone. Hypothesis 2 is that, relative to HABITs, participants in HABITs + Texts will exhibit improved sleep and circadian functioning. We hypothesize that this effect will be observed from pre-treatment to post-treatment, pre-treatment to 6-month follow-up, and pre-treatment to 12-month follow-up.

Aim 3 is to assess if adding a text message intervention to HABITs improves functioning in the five health-relevant domains in the short (post-treatment) and longer term (6-month and 12-month follow-up), relative to HABITs alone. Hypothesis 3 is that, relative to HABITs, participants in HABITs + Texts will exhibit lower health risk. We hypothesize that this effect will be observed from pre-treatment to post-treatment, pre-treatment to 6-month follow-up, and pre-treatment to 12-month follow-up.

As an Exploratory Aim 1, comparing HABITs and HABITs + Texts, we will examine (a) if the strength of sleep health behavior habit formation mediates the effects of the intervention (specifically by adding the text intervention to HABITs) on improvement in sleep and circadian outcomes, and health-relevant domain outcomes, and (b) if intervention effects are moderated by selected variables (i.e., age, sex, and socioeconomic status).

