#### Secondary measures

##### Adapted self-report habit index – primary bundle to build (Adapted SRHI—Primary)

The Adapted SRHI—Primary will assess the habit strength of the primary bundle to build at each session during treatment, post-treatment, 6-month, and 12-month follow-up assessments. The original Self-Report Behavioral Automaticity Index (SRBAI) [70] is a 4-item automaticity-specific adaptation of the full Self-Report Habit Index (SRHI) [88]. The four items of the original SRBAI plus two items from the full 12-item SRHI (“I do frequently” and “That belongs to my (daily, weekly, monthly) routine”) will be added to assess the frequency and relevance to self-identity, the two other primary proposed characteristics of habit, in addition to automaticity [70]. In total, six items will each be rated on a 5-point Likert scale (1 = *strongly disagree*, 5 = *strongly agree*). Total sum scores range from 6 to 30, where higher scores indicate greater habit strength.

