#### Other measures

##### Adapted self-report habit index – secondary bundle to build (Adapted SRHI—Secondary)

The Adapted SRHI—Secondary will assess the habit strength of the secondary bundle to build at each session during treatment, post-treatment, 6-month, and 12-month follow-up assessments. This measure is comprised of 1-item from the original Self-Report Behavioral Automaticity Index. Based on previous research [70], the 1-item selected, “I do automatically,” has been shown to have adequate face validity based on expert ratings. The 1-item will be rated on a 5-point Likert scale (1 = *strongly disagree*, 5 = *strongly agree*), where higher scores indicate greater habit strength.

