### Changes to preregistration

This study was preregistered on clinicaltrials.gov (identifier: NCT05167695) on December 22, 2021. Since the study start date (May 2022), six updates have been made to clinicaltrials.gov: (1) EMA data was removed from the 6-month and 12-month follow-up due to participant burden and insufficient resources, (2) sessions 4 to 9 of treatment could not be completed in 20 min and thus were updated to 30-min sessions, (3) two additional outcome measures were added as it became clear that participants were typically working on at least two habit bundles (i.e., Adapted SRHI for the primary and secondary habit bundles), (4) an additional outcome was added as a manipulation check (i.e., Proportion of Text Messages Read), (5) the inclusion criteria for eveningness was clarified to distinguish “night-to-night variation in sleep and wake times” as opposed to “sleep/wake times”, and (6) we removed season as a moderator as there is little empirical evidence to support or negate the role of season in treatment response. This decision also served to help minimize multiple comparisons.

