### Aims 1–3: Effectiveness outcomes of HABITs versus HABITs + Texts

For Aims 1–3, we will use intent-to-treat analyses, including all randomized participants as randomized in the analysis regardless of their adherence or completion of the assigned intervention. We will use multilevel modeling [120] to account for multiple observations over time (pre-treatment, post-treatment, 6-month, and 12-month follow-up) nested within participants. The level 1 equation captures within-person variation across time and will include dummy-coded time indicators (0 = pre-treatment, 1 = post-treatment, 2 = 6-month follow-up, 3 = 12-month follow-up) as predictors. The level 2 equation captures between-person variations in the intercept and slope of time and will include dummy-coded intervention condition (0 = HABITs, 1 = HABITs + Texts) and intervention-by-time interaction terms, as predictors. The parameters of interest will be significant intervention-by-time interactions at the 5% level (i.e., differences in intervention effects on change in outcomes from pre-treatment to post-treatment, pre-treatment to 6-month follow-up, and pre-treatment to 12-month follow-up). Significant intervention-by-time interactions indicate that the trajectory of change on outcomes is significantly different over time, comparing HABITs + Texts to HABITs. For Aim 1a, utilization of sleep health behaviors, as indexed by the Utilization Scale will be modeled as the continuous outcome variable. For Aim 1b, sleep health behavior habits, as indexed by the primary measure (SRBAI-US), secondary measure (Adapted SRHI – Primary), and other measure (Adapted SRHI – Secondary), will be modeled as the continuous outcome variables, separately. For Aim 2, sleep and circadian functioning, as indexed by primary measures (i.e., CSHS, CSM, PROMIS-SRI, and PROMIS-SD) and secondary measures (i.e., PSQI, Sleep Diary and Actigraphy [night-to-night variability in the mid-point of sleep]) will be modeled as the continuous outcome variables, separately. For Aim 3, the latent variables of health risk, as indexed by the primary measure (Adapted WSAS) and secondary measures (i.e., DASS, PROMIS-CF, BSSS, PROMIS-APS, PHQ, and EMA Composite Risk Score^8^), will be modeled as the continuous outcome variables, separately.

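### Two non-primary Aim 1b outcomes (Adapted SRHI – Primary and – Secondary) are given change-from-pre-treatment contrasts but are not measured at pre-treatment

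*Protocol article*

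**What the plan says.** All statements are in the protocol article.

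- **Model.** The section on Aims 1–3 under Planned analyses specifies "dummy-coded time indicators (0 = pre-treatment, 1 = post-treatment, 2 = 6-month follow-up, 3 = 12-month follow-up) as predictors".
- **Parameters of interest.** The same section names the intervention-by-time interactions, defined as "differences in intervention effects on change in outcomes from pre-treatment to post-treatment, pre-treatment to 6-month follow-up, and pre-treatment to 12-month follow-up".
- **Outcomes.** For Aim 1b the model is applied to the primary measure, SRBAI-US. The text then adds that the "secondary measure (Adapted SRHI – Primary), and other measure (Adapted SRHI – Secondary), will be modeled as the continuous outcome variables, separately".
- **Hypothesis.** The Aims section puts Hypothesis 1b in the same terms: "We hypothesize that these effects (1a and 1b) will be observed from pre-treatment to post-treatment, pre-treatment to 6-month follow-up, and pre-treatment to 12-month follow-up".
- **Schedule, Adapted SRHI – Primary.** Its description says that it "will assess the habit strength of the primary bundle to build at each session during treatment, post-treatment, 6-month, and 12-month follow-up assessments".
- **Schedule, Adapted SRHI – Secondary.** Its description says that it covers the "habit strength of the secondary bundle to build at each session during treatment, post-treatment, 6-month, and 12-month follow-up assessments".
- **Table 4.** The pre-treatment cell is empty for both Adapted SRHI measures. It is marked for SRBAI-US.

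The Measures section gives a default schedule that includes pre-treatment, but only where nothing else is specified. For these two measures something else is specified. The HABITs section places the derivation of the habit bundles in sessions 1–3.

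**The concern.** The plan assigns both Adapted SRHI measures by name to a model whose reference occasion they lack. The empty cells in Table 4 are not a slip, because the object being rated does not exist until the early sessions have produced it. A change from pre-treatment therefore has no meaning for these scores.

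The analyst will have to choose another reference or another contrast, and the plan does not say which. The candidates estimate different things: a difference between arms at a visit, a change from some treatment session, or a change after treatment has ended. If the choice is made once data are in hand, it can depend on the results. These two measures are the scales in the plan that rate each participant's own bundles, which the texts are written to support. SRBAI-US rates 16 behaviors common to all participants. A clear prespecified analysis of the Adapted SRHI is therefore worth having.

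**Working it through.** The plan states no figure on this point. The question is whether the named contrasts are estimable.

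**Inputs**

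- Occasions in the model: pre-treatment (0), post-treatment (1), 6 months (2), 12 months (3), from the section on Aims 1–3.
- Fixed effects: intercept; time dummies T1, T2, T3; arm A; interactions A×T1, A×T2, A×T3 (same section). Sex and age as stratification factors come from Preliminary analyses and missing data. Each factor is taken here as a two-level term, which gives 10 columns.
- Occasions at which both Adapted SRHI measures are collected and the model has a time level: 1, 2 and 3. Treatment-session ratings exist, but the model has no time level for them.

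**Step 1: outcomes with a pre-treatment value, such as SRBAI-US.** With occasions 0 to 3 the design has rank 10 of 10. All three interactions are estimable.

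**Step 2: Adapted SRHI, occasions 1 to 3 only.** Every row now belongs to exactly one of the three later occasions, so two identities hold on every row:

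- T1 + T2 + T3 = 1, which is the intercept column.
- A×T1 + A×T2 + A×T3 = A, which is the arm column.

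These are two exact dependencies, so the rank is 10 − 2 = 8. A numerical check with 160 participants gave rank 8 of 10 and found none of the three interactions estimable.

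**Step 3: why the interactions are lost.** Let a be the arm coefficient and b1, b2, b3 the interactions. The data inform only the arm differences at each visit:

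- post-treatment: a + b1
- 6 months: a + b2
- 12 months: a + b3

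Adding any constant c to a and subtracting c from b1, b2 and b3 leaves all three sums unchanged. The values of b1, b2 and b3, which are the stated parameters of interest, are therefore arbitrary. This happens for two measures with three contrasts each: 2 × 3 = 6 contrasts.

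**Step 4: what remains estimable.** The three visit-specific arm differences do. So do the differences b2 − b1 and b3 − b1, which are arm differences in change after post-treatment. The count agrees with the rank: 3 visit means + 3 arm differences + 2 stratification terms = 8.

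**Step 5: post-treatment as a substitute reference.** Suppose the arm difference is δ at all three visits. The arm term is then δ, and the two remaining interactions are δ − δ = 0. A fully maintained effect would sit in the arm term and not in the interactions that the plan designates as the test.

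**Step 6: missing-data methods.** Maximum likelihood and multiple imputation do not supply the reference. The pre-treatment value is absent by design for every participant, so there are no observed values from which to model it.

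**The case against.** The strongest reply is that the damage is small and the article is condensed. One general model is stated for outcomes with differing schedules; actigraphy and the EMA score also lack some of its occasions. Only one secondary and one other measure are affected. SRBAI-US carries Aim 1b and the mediation analysis, Exploratory Aim 2 uses the primary measures, and the sample size does not rest on the Adapted SRHI. The scope argument stands in full. The condensation argument does not: the article names these measures, the model, the reference and the contrasts, and they are incompatible. Actigraphy and EMA are collected at pre-treatment and so keep the reference and the pre-to-post contrast; the Adapted SRHI measures lose all three.

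A reader might infer more than the article supports:

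- **That Aim 1b cannot be tested.** It can, through SRBAI-US.
- **That the analysis as written would turn a real effect into a null result.** As written it yields no estimate. The zero in Step 5 requires post-treatment to be substituted as reference, which the article does not state.
- **That the Adapted SRHI – Primary is the only rating of a participant's own target habit.** The Secondary version rates another of the participant's own bundles, and the texts address both.
- **That early participants have no ratings.** Changes to preregistration says that "two additional outcome measures were added as it became clear that participants were typically working on at least two habit bundles". It lists this as a registry update made after the study start, without a date, and does not say when collection of the ratings began or that anyone lacks them.
- **That the session 3 rating is the natural baseline.** Bundles are derived across sessions 1–3 and refined in sessions 4–9, so it is not shown that this rating concerns the same settled bundle. Randomization precedes session 1, participant and coach write the texts together, and blinding is stated for assessors only. Identical experience in the two arms up to session 3 is therefore an assumption.

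**Conclusion.** The point holds for Adapted SRHI – Primary (secondary outcome) and Adapted SRHI – Secondary (other outcome). For each, all three pre-treatment-referenced arm-by-time contrasts are non-estimable, six in total. This is an internal contradiction in a stated analysis, not a detail left to another document. No primary outcome is touched, and the data already scheduled support a valid randomized comparison at each later visit.

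The conclusion rests on reading Table 4 and the two measure descriptions as complete schedules. It does not depend on the number of participants, on how sex and age are coded, or on the random-effects structure. Footnote texts were not available; in the section on Aims 1–3 the only footnote marker in the outcome list is on the EMA score.

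**What to change.** For these two outcomes only:

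1. Replace the change-from-pre-treatment contrasts with prespecified between-arm differences at post-treatment, 6 months and 12 months. Use a model with a three-level visit factor, arm, arm-by-visit terms and the stratification factors. Randomization supports this comparison without a baseline rating.
2. Optionally adjust for a treatment-session rating taken before texting starts. Name the session in advance, and use it only if it rates the same bundle that is rated later.
3. State that the tests are the visit-specific arm differences, so that software does not make post-treatment the reference by default.
4. In the Aims section, limit the change-from-pre-treatment wording of Hypothesis 1b to SRBAI-US, and state the visit-wise form for the two Adapted SRHI measures.
5. Report how many participants in each arm have ratings on each Adapted SRHI measure at each visit.

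The cost is analysis wording, settled before outcome data are examined by arm. No new assessment is needed, because the ratings at all three visits are already scheduled. Adding a pre-treatment rating would not help, since the bundles are not yet defined at that assessment.

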### Sensitivity analyses

Two sets of sensitivity analyses will be run to account for complexities that may be relevant to outcomes of Aims 1–3. One set of sensitivity analyses will be run to help account for the complexities related to the texting intervention. These analyses will be conducted to account for the proportion of text messages each participant read. We will also account for those who did not receive the messages due to a logistical or technical issue (e.g., technical issues with EZ Texting, mobile device issues). In the second set, sensitivity analyses will be conducted to account for (a) participants’ perceptions of the intervention credibility and expectancy and (b) adverse events experienced during the intervention. In other words, these analyses will test the effectiveness of HABITs in various participant experiences, as perception [111] and adverse experiences may impact intervention effectiveness [112, 113].

### Exploratory aim 1: mediators and moderators of intervention effects

Structural equation modeling [121] will be used to test whether sleep health behavior habit formation, as indexed by the SRBAI-US, mediate the effects of the intervention (HABITs vs. HABITs + Texts) on improving sleep and circadian functioning and health-relevant risk, as indexed by the primary measures for each. Bootstrapping procedure with 5000 replications will be used to test the statistical significance of the indirect effect from intervention condition to outcomes via the mediator [122]. The Benjamini–Hochberg procedure [123] will be used to correct for multiple testing on the outcomes (i.e., sleep and circadian functioning and health-relevant risk) [124]. Moderators will be assessed using a three-way interaction, intervention-by-time-by-moderator, in the multilevel model described in Aims 1–3. Each moderator and outcome will be tested in a separate model. Moderators will include age group (older adolescents 18–20 years of age vs. emerging adults 21–30 years of age), sex (sex assigned at birth; male, female, prefer not to say), and socioeconomic status (income; in 10,000 increment buckets [e.g., 0–10,000]).

### Exploratory aim 2: effectiveness outcomes of HABITs across HABITs and HABITs + Texts

Should the HABITs versus HABITs + Texts intervention effects (Aims 1–3) or the within-group pre-post-treatment effects of HABITs be non-significant we will conduct exploratory analyses combining the two randomized groups (HABITs and HABITs + Texts) to evaluate if HABITs (regardless of whether the text message intervention is added) is associated with an improvement in the utilization of sleep health behavior, sleep health behavior habits, sleep and circadian outcomes, and the five health-relevant domain outcomes in the short (post-treatment) and longer term (6-month and 12-month follow-up), relative to pre-treatment. Multilevel modeling [120] will be used to account for multiple observations over time (pre-treatment, post-treatment, 6-month, and 12-month follow-up) nested within participants. The fixed component of the model captures within-person variation across time and will include dummy-coded time indicators (0 = pre-treatment, 1 = post-treatment, 2 = 6-month follow-up, 3 = 12-month follow-up). The model will control for stratification factors (i.e., sex, age) used during the randomization procedure. The parameter of interest will be significant coefficient of time at the 5% level. Significant coefficient of time indicates that the combined intervention effect is significantly different across time, with pre-treatment as the reference group. Specifically, we will test change in outcomes from pre-treatment to post-treatment, pre-treatment to 6-month follow-up, and pre-treatment to 12-month follow-up. Each outcome, utilization of sleep health behaviors, sleep health behavior habits, sleep and circadian functioning, and the latent variable of health risk, as indexed by the primary measures, will be modeled as the continuous outcome variables.

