**Methods:**

Participants (*N* = 160) will be randomly allocated to HABITs and HABITs + Texts. Both interventions include HABITs which involves three 50-min sessions followed by six 30-min sessions. Alongside the latter six sessions, HABITs + Texts will concurrently receive the text message intervention. Aims 1–3 will compare HABITs + Texts to HABITs on improvements in the outcomes of (1) utilization of sleep health behaviors and habit formation, (2) sleep and circadian functioning, and (3) functioning in five health-relevant domains, in the short (post-treatment) and longer (6-month and 12-month follow-up) term. Exploratory analysis will (1) compare HABITs and HABITs + Texts on (a) if sleep health behavior habit formation mediates the effects of intervention on improvement in outcomes and (b) if intervention effects are moderated by select variables, and (2) to evaluate if HABITs (regardless of the text message intervention) is associated with an improvement in outcomes in the short and longer term.

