Lastly, should the HABITs versus HABITs + Texts intervention effects be non-significant, we will conduct Exploratory Aim 2: an analyses combining the two randomized groups (HABITs and HABITs + Texts) to evaluate if HABITs (regardless of whether the text message intervention is added) is associated with an improvement in the utilization of sleep health behaviors, sleep health behavior habits, sleep and circadian outcomes, and health-relevant domain outcomes in the short (pre-treatment to post-treatment) and longer term (pre-treatment to 6-month and 12-month follow-up).

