### Participants

The inclusion criteria will be as follows: (1) age between 18 and 30, (2) risk for eveningness chronotype: scoring less than or equal to 26 on the Composite Scale of Morningness or a mid-point of sleep later than 4:30 a.m. for 18–24 years of age and 3:50 a.m. for 25–30 years of age on work-free/weekend days over the past month or night-to-night variation in sleep and wake times across one month of 2 h or more, (3) at risk in one of the five health domains: the emotional, cognitive, behavioral, social, or physical domain (at risk is defined as scoring 4 or higher on one item from the Adapted Version of the Work and Social Adjustment Scale), (4) English language fluency, (5) able and willing to give informed consent, and (6) if taking medication for sleep, the dose and frequency of use must have been stable for at least 4 weeks.

Participants will be excluded if they meet any of the following criteria: (1) presence of substance abuse/dependence, mental illness, physical illness, suicidality, or developmental disorder only if it makes participation in the study unfeasible or if there is a significant risk of harm and/or decompensation if treatment of that comorbid condition is delayed due to participating in this study, (2) evidence of sleep apnea, restless legs, or periodic limb movements during sleep (participants presenting with provisional diagnoses of any of these disorders will be referred for a non-study polysomnography evaluation and will be enrolled only if the diagnosis is disconfirmed or if the disorder is treated), (3) night shift worker where the shift is scheduled between the hours of midnight to 6:00 a.m. more than two nights per week, and (4) pregnancy or breast-feeding.

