## Discussion

This study aims to evaluate the Habit-based Sleep Health Intervention (HABITs) and whether adding a text message intervention helps young adults to form habits that modify the psychosocial and behavioral contributors to eveningness. By integrating the science on habits and learning theory with behavior change interventions, the aim is to help recipients turn new behaviors into habits and thereby increase the benefits of the intervention in both the short and longer term [42]. Additionally, the text message intervention has great potential because it is a low-cost, efficient, and potent intervention that may help habit formation and bolster the maintenance of behavior change [62–64]. We will investigate if this approach improves the utilization of sleep health behaviors, sleep health behavior habits, sleep and circadian functioning, and functioning in five health-relevant domains.

The findings have the potential to advance knowledge and address several research areas and priorities. First, this study will demonstrate whether leveraging the science of habits can be translated into effects on sleep and circadian functioning and health-relevant outcomes. Importantly, the habit formation approach is potentially “transdiagnostic” (relevant to a broad range of problems) and “pantreatment” (relevant to a broad range of types of treatment) [42]. Thus, evaluating this strategy may help other scientists improve interventions and outcomes for a variety of populations and settings. Second, this study will contribute to literature evaluating the use of a low-cost and efficient text message intervention, grounded in learning theory, to bolster habit formation and maintenance. Third, by focusing on participants with an eveningness chronotype, the present study will add to the literature on how addressing eveningness may improve outcomes in the short and longer term. The latter is particularly important given eveningness’ adverse health consequences and the limited research on interventions to address it. Fourth, this study will contribute to knowledge on the processes of behavior change during emerging adulthood, which is often marked by a shift in priorities toward self-sufficiency and personal responsibility. Therefore, advancing the understanding of processes related to the formation and maintenance of helpful behaviors is particularly important for the developmental period spanned by the study sample.

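### Exploratory Aim 2 carries three different run conditions, one of which pools arms just found to differ, and it reads an uncontrolled change over time as an intervention effect

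*Protocol article*

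**What the plan says.** The protocol article states when the pooled analysis is run in three places.

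- Abstract, Methods: no condition. An exploratory purpose is "to evaluate if HABITs (regardless of the text message intervention) is associated with an improvement in outcomes in the short and longer term".
- Aims: "should the HABITs versus HABITs + Texts intervention effects be non-significant, we will conduct Exploratory Aim 2". Only the arm comparison is named.
- Exploratory aim 2 section: after naming the arm comparison, it continues "or the within-group pre-post-treatment effects of HABITs be non-significant we will conduct exploratory analyses combining the two randomized groups". The within-group change under HABITs is now an alternative trigger.

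The model in the Exploratory aim 2 section contains dummy-coded time indicators and the stratification factors sex and age; no arm or arm-by-time term is listed. Its reading rule is "Significant coefficient of time indicates that the combined intervention effect is significantly different across time, with pre-treatment as the reference group". The test is at the 5% level.

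Both arms receive HABITs (Intervention, Table 1). Under Participants, "at risk is defined as scoring 4 or higher on one item from the Adapted Version of the Work and Social Adjustment Scale", and a Composite Scale of Morningness (CSM) score of 26 or less is one of three alternative eveningness routes. The Adapted WSAS total and the CSM are both primary measures (Table 4). The Discussion says that "this study will demonstrate whether leveraging the science of habits can be translated into effects on sleep and circadian functioning". Its limitations explain the absence of a placebo-text arm but do not mention the absence of a comparator without HABITs.

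**The concern.** Two things are fixed badly.

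First, the rule for running the analysis differs by place, and the longest version brings in a case where pooling makes no sense. If the arms have been shown to differ, a single time coefficient averages two different changes, yet it is to be reported as the result for HABITs regardless of texts.

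Second, the reading rule exceeds the design. Randomisation here isolates the texts. Nothing in the trial isolates HABITs, so change from pre-treatment mixes any HABITs effect with everything else that changes over 12 months.

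At stake is what the trial may say about HABITs if the texts add nothing, which is when this analysis becomes the main positive message.

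**Working it through.** **1. Triggers, case by case**

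| Arm comparison | Change under HABITs alone | Abstract | Aims | Exploratory aim 2 section |
|---|---|---|---|---|
| non-significant | either | run | run | run |
| significant | non-significant | run | not called for | run |
| significant | significant | run | not called for | not called for |

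The Aims and Exploratory aim 2 sections differ only in the second row. The change under HABITs alone is also not among the parameters of interest named for Aims 1–3, which are the intervention-by-time interactions.

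**2. What pooling reports in the second row**

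Let c be the change under HABITs and c + δ the change under HABITs + Texts. With 1:1 allocation and similar attrition, the pooled time coefficient is c + δ/2. Take the d = 0.60 of the Sample size section as δ, in units of the SD of change, and c = 0. The pooled change is 0.30, all of it due to texts. Standardised in the mixed group it is 0.30/√(1 + 0.30²) = 0.29. With 128 people, a standardised change of 0.25 already has 80% power.

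**3. How large could change be with no intervention effect?**

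The protocol gives no figure for this aim, so there is none to reproduce. The inputs are n = 128 (160 recruited less 20%; Sample size) and a 5% two-sided test (Exploratory aim 2 section). Assumed, because the protocol does not give them: retest correlation r, where each cut lies in the screened population, and inter-item correlation.

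If the score that selects is also the analysed baseline, with selected mean m and variance v in SD units:

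- regression to the mean = (1 − r)m
- SD of change = √(1 − r² + (1 − r)²v)
- dz = the first divided by the second; the paired t-test has non-centrality dz√128 = 11.31·dz

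(a) *Worse half on the outcome itself:* m = 0.80, v = 0.36.
- r = 0.7: 0.24/0.74 gives dz = 0.32, significant in about 95% of trials.
- r = 0.8: 0.16/0.61 gives dz = 0.26, about 83%.

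(b) *Any one of five items above its median, outcome the total (the form of the Adapted WSAS rule):* by simulation, m = 0.18 and v = 0.77 at inter-item correlation 0.3; m = 0.28 and v = 0.68 at 0.5.
- Smallest case (0.3, r = 0.8): 0.036/0.625 gives dz = 0.057, about 10%.
- Largest case (0.5, r = 0.7): 0.083/0.756 gives dz = 0.110, about 24%.

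(c) *Screening score and baseline are separate measurements, equally correlated with each other and with post-treatment:* expected change is zero and the rate is the nominal 5%.

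The Procedure describes an eligibility phone screen followed by a pre-treatment assessment, but does not say which scores decide entry. So (c) cannot be excluded, and neither can (a) or (b).

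**4. Which outcomes are exposed**

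Regression to the mean applies directly to two of the seven primary measures, CSM and Adapted WSAS. The CSM effect is diluted because CSM is one of three routes. The Composite Sleep Health Score overlaps with entry criteria only through sleep timing and regularity. Maturation is a separate matter: the Background puts the peak of eveningness at about 16–20 years, while participants are 18–30 and followed for 12 months. The protocol gives no rate of change from which to size it.

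**The case against.** The case for leaving the text alone is fair in several respects. The analysis is labelled exploratory, and its question is whether HABITs is associated with improvement. Directly after the reading rule, the section says that change from pre-treatment is what will be tested. An abstract commonly drops a condition. The trigger in Aims is contained in the wider one, and neither says that the analysis runs only then. With 1:1 allocation, the pooled coefficient and an arm-averaged contrast give nearly the same estimate. All of this stands and lowers the severity. It does not remove the second row of the table or the reading rule itself.

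Three stronger readings are tempting, and the documents do not support them.

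- *A significant pooled result is near certain whether or not HABITs works.* That needs the selecting score to be the analysed baseline and entry to take the worse half or fewer on that very outcome. The protocol states neither, and five of the seven primary measures are not entry scales.
- *Pooling enlarges the sample until significance is reached.* It is a single, openly stated pooling step, not repeated testing.
- *The Discussion announces that HABITs works.* It says the study will show whether this is so. The difficulty is narrower: both arms receive the habit component, so the randomised comparison cannot answer that question.

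**Conclusion.** The point holds as a fault in an exploratory analysis; Aims 1–3 are unaffected. Two parts rest on the text alone: the run condition differs between places, with one case in which differing arms are pooled without an arm term, and an uncontrolled change is given the name of an intervention effect. The size of the second problem cannot be fixed from the protocol. With no intervention effect, the false-positive rate for a measure used at entry is about 5% if screening and baseline are separate measurements. It is about 10–24% under the any-one-of-five-items rule at a median cut, and 83–95% if the worse half on the outcome is selected on the baseline score itself. All three rest on an assumed retest correlation of 0.7–0.8 and, in the second case, an inter-item correlation of 0.3–0.5. The change matters because it settles what the trial may conclude about HABITs.

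**What to change.** 1. Drop both triggers. Run the analysis once, unconditionally, as arm-averaged time contrasts (post-treatment, 6 and 12 months against pre-treatment) from the Aims 1–3 model, keeping arm and arm-by-time. Show the arm-specific changes beside the average: where the arms differ, the average still contains half the text effect, and the reader must be able to see that.
2. In the reading rule, replace the reference to a combined intervention effect with *within-person change from pre-treatment, uncontrolled*.
3. Give the same statement in the abstract, the Aims and the Exploratory aim 2 section.
4. Add the missing no-HABITs comparator to the limitations. Name maturation as a competing explanation and, for CSM and Adapted WSAS if the selecting score also serves as baseline, regression to the mean.
5. Limit the Discussion claim to the added effect of texts, with change under HABITs described only.

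The cost is wording and one contrast from a model already planned; no new data are needed. The downside is a weaker fallback claim if the texts add nothing. The change should be made before any arm comparison is seen.
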